### Data Management

The Trial Management Group (TMG) consists of the principal investigator (FD) and associated investigators (GG and MG). All adverse events will be reviewed by the TMG and reported to the ethics committee. The process of recruitment and data management will be overseen by the TMG. The data will be securely entered and stored on the University of Queensland Data Manager repository. This trial may be subject to random auditing by the ethics committee. All protocol amendments will be reported to the ethics committee.

### Statistical Analysis

Participants’ medication dosages will be converted to olanzapine equivalents [54]. Outcome measures will be analyzed using the SPSS (version 27 or higher; IBM Corp) software package. A series of 2 (group: intervention and patient control) x 2 (time: baseline and postintervention) mixed factorial ANOVAs will be conducted to evaluate the treatment group differences for each of the outcome measures. If the normality assumption is violated, nonparametric analyses will be conducted.

For the fMRI analysis, standard preprocessing of the functionally weighted images will be carried out using the Statistical Parametric Mapping Version 12 [55]. The preprocessing steps follows: slice timing on the functional images, to correct for differences in slice acquisition times within each volume using the middle slice as reference; realignment (estimate and reslice) on the functional images, to correct for interscan movement within each run (defined as >3 mm translation and >2 degrees rotation); coregistration of the functional and structural images; segmentation of the structural image, with heavy regularization (0.1) recommended for MP2-RAGE sequence; normalization of the resliced images into a standardized, stereotaxic space (according to the Montreal Neurological Institute template); and smoothing of normalized images with a 8 mm full-width-at-half-maximum isotropic Gaussian kernel.

The general linear model approach for event-related designs will be conducted using the Statistical Parametric Mapping Version 8 [55]. For the first-level analysis, task-related changes in the blood-oxygen-level dependent signal will be estimated at each voxel for each participant. Head motion parameters will be included as a regressor to account for participant motion during the experiment. A 1/128 Hz high-pass filter will be used to remove slow signal drifts, and a canonical hemodynamic response function with no derivatives will be selected.

Computational modeling will allow the estimation of learning parameters at each point in time, during each task condition, for each participant. We will use a variational Bayesian framework to compute how the value of each button was estimated based on the behavioral choices made and feedback received. This allows us to measure how learning occurred during the experimental task and the subprocesses that must underlie this learning. Second-level group analyses will examine how learning in patients differs from that observed in control participants and how CR therapy alters learning efficiency and the underlying neural activity. We will correct for multiple comparisons; the voxel-level threshold will be set at P<.05 family-wise error corrected.

### Ethical Considerations

This trial has been approved by the Metro South Health Human Research and Ethics Committee (HREC/2021/QMS/67093). All protocol modifications and serious adverse events will be reported to the ethics committee. The study will be conducted in accordance with the Declaration of Helsinki and Good Clinical Practice guidelines. All participation will be based on voluntary, written, and informed consent. Participants with serious mental illness can be challenging to follow up with; thus, the researchers will make multiple attempts to contact each participant at baseline and postintervention. In cases of deterioration in mental state, the intervention will be discontinued, and the participant’s treating team will be advised. Participants will be able to withdraw at any point in the study. All data used for analysis will be deidentified.

## Results

This trial was registered in August 2018 and commenced recruiting in May 2022. As of September 2023, we have enrolled 11 healthy controls. We have also enrolled 16 individuals with SSDs, 15 into the CR group, and 1 into the TAU group. The projected completion of recruitment is September 2024. The projected final reporting date is September 2025. Results will be disseminated to mental health clinicians, researchers, and key stakeholders through peer-reviewed publications and presentations. In-kind funding is being provided by Metro South Addiction and Mental Health Services and the Translational Research Institute. This study received an Extraordinary Research Grant from the Princess Alexandra Hospital Research Foundation to assist with the purchase of fMRI scans in May 2023.

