**Results:**

As of September 2023, this study has enrolled 15 participants in the CR group, 1 participant in the treatment-as-usual group, and 11 participants in the healthy control group. Recruitment is expected to be completed by September 2024. Data analysis is expected to be completed and published in early 2025.

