## Methods

### Study Design

The study is a nonrandomized clinical pilot trial to investigate whether reward processing pathways are involved in the mechanism of action of cognitive remediation therapy (Computerized Interactive Remediation of Cognition-Training for Schizophrenia [CIRCuiTS]) [30,31]. We will recruit 3 participant groups: 20 participants with SSDs who will complete the CR program (the intervention group), 20 participants with SSDs who will receive TAU, and 20 matched healthy control participants. Figure 1 depicts a schematic of the study design.

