### Participants

A total of 40 participants with a diagnosis of an SSD will be recruited from the Metro South Addiction and Mental Health Service community teams (Brisbane, Australia). Given that this is a pilot study, a power analysis was not conducted [32]. Instead, the sample size was informed by practical factors relating to the project, including the budget, the availability of CR facilitators, and the recruitment and attrition rates from our previous studies. This sample size is also consistent with other research in this area [33].

The inclusion criteria for the intervention and TAU groups and the healthy control group, as well as the exclusion criteria for all groups, have been provided in Textbox 1.

The inclusion and exclusion criteria.

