**Exclusion criteria for all groups**
Metallic object in their body (eg, cardiac pacemaker and cochlear implant)Pregnant or possibly pregnant (unprotected sex since last menstrual period)History of claustrophobiaPermanent metal dental appliancesBodyweight ≥120kg

The researchers will obtain consent from all participants through a participation information and consent form. For participants with SSDs, half (n=20) will complete CR and form the intervention group. Those participants with SSDs (n=20) that are not interested in completing CR will form the patient TAU group and will complete the pre- and postmeasures only. Thus, group allocation will be based on an individual’s preference to participate in CR. In addition, matched healthy controls (n=20) will be recruited from the Metro South Addiction and Mental Health community services in the Princess Alexandra Hospital district as well as from the general population. We do not anticipate that it will be difficult to collect these healthy controls, given our already established connections with other researchers and staff within this district. Therefore, we expect to be able to recruit this group through word of mouth and the snowball effect. These health controls will have no history of SSDs. This will provide a benchmark to compare the clinical groups. Hence, the total number of participants for the study is 60.

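### At the observed pace and split (15 CR, 1 TAU), 20 versus 20 by September 2024 is out of reach, and the between-group parts of Hypotheses 2-4 depend on the TAU group

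*Protocol article*

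**What the plan says.** The Study Design section sets the group sizes: 20 patients with schizophrenia spectrum disorders (SSD) on CR, "20 participants with SSDs who will receive TAU, and 20 matched healthy control participants". The Participants section says where the TAU group comes from: "Those participants with SSDs (n=20) that are not interested in completing CR will form the patient TAU group". It adds that "group allocation will be based on an individual’s preference to participate in CR". The same section explains that practical considerations set the sample size, among them recruitment rates in the team's previous studies, and that "Given that this is a pilot study, a power analysis was not conducted".

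The Results section gives the status. The trial "commenced recruiting in May 2022. As of September 2023, we have enrolled 11 healthy controls", and for patients: "We have also enrolled 16 individuals with SSDs, 15 into the CR group, and 1 into the TAU group". It then states: "The projected completion of recruitment is September 2024". The abstract gives the same counts and the same date ("Recruitment is expected to be completed by September 2024").

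The article does not comment on the 15:1 split. Its Limitations section discusses self-selection as a possible bias and an intention to match the two patient groups, but not a shortfall in one of them.

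**The concern.** Allocation by preference does not control the group ratio, yet the plan fixes the ratio at 1:1. The trial's own counts show preference running 15 to 1 towards CR, and the stated size and date are left unchanged beside those counts.

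The TAU group carries the comparison with CR in the primary aim, the comparator in Hypothesis 2, and the contrast in Hypotheses 3 and 4, where mediation is expected in the CR group but not in the patient control group. It is also one of the two levels of the group factor in every 2 x 2 mixed ANOVA in the Statistical Analysis section. If it closes with a handful of people, those analyses can still be run but will say very little, and the article gives no rule for reporting them in that case.

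**Working it through.** **Inputs.** From Study Design: target 20 CR and 20 TAU. From Results: 15 CR, 1 TAU and 11 healthy controls by September 2023; recruitment opened May 2022; end projected for September 2024. I take 16 months elapsed (15-17 depending on the days) and 12 months left (12-13). The article gives no alpha, power, effect size or standard deviation, so 20 per group cannot be reproduced from a formula. Only the sums can be checked: 15 + 1 = 16 and 20 + 20 + 20 = 60, and both agree.

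**Step 1: rate needed against rate observed.**
- TAU still needed: 20 - 1 = 19, so 19/12 = 1.58 per month.
- TAU observed: 1/16 = 0.0625 per month.
- Ratio: 1.58/0.0625 = 25.3 (22 to 27 over the plausible month counts).
- All SSD still needed: 5 CR + 19 TAU = 24, so 24/12 = 2.0 per month, against 16/16 = 1.0 observed.

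Meeting the target therefore needs overall patient accrual to double and the split to turn from 15:1 to 5:19.

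**Step 2: what the observed TAU rate predicts.**
- Expected further TAU: 12 x 1/16 = 0.75, a final group of about 2.
- Exact Poisson 95% upper limit for a count of 1 is 5.57, so the upper limit on that mean is 5.57 x 12/16 = 4.2.
- With uncertainty in the rate allowed for (gamma-Poisson prediction, Jeffreys prior), the chance of 19 or more further TAU is at most about 2 in a million.

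**Step 3: the same question through the split.**
- TAU share: 1/16 = 6.25%, exact 95% interval 0.2% to 30.2%.
- At the upper limit, with the 16 already enrolled taken as known, the next 24 SSD enrolments give 1 + 0.302 x 24 = about 8 TAU in total.
- If the true split were 50:50, the chance of one or fewer TAU in 16 would be 0.0003.

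**Step 4: most favourable ordering at the observed pace.** Suppose every further SSD enrolment goes to TAU at 1 per month. TAU then reaches 1 + 12 = 13 (12 to 15 over the month ranges) and CR stays at 15. This is still not 20 versus 20.

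**Step 5: is the whole trial behind?** Healthy controls at their own pace reach 11 + 12 x 11/16 = about 19. The shortfall lies in the patient groups, chiefly TAU.

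**Step 6: effect on the contrast.** With a common standard deviation of the change score, the standard error of the CR-TAU difference is sqrt(1/n1 + 1/n2) in units of that SD.

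| CR vs TAU | SE | Relative to 20 vs 20 |
|---|---|---|
| 20 vs 20 | 0.316 | 1.0 |
| 15 vs 13 | 0.379 | 1.2 |
| 20 vs 10 | 0.387 | 1.2 |
| 20 vs 5 | 0.500 | 1.6 |
| 20 vs 2 | 0.742 | 2.3 |

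For mediation within the patient control group, two participants cannot support a path: a line with intercept and slope passes exactly through two points and leaves no residual degrees of freedom.

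**The case against.** **It is a projection.** Step 2 assumes a constant TAU rate. The grant towards scans came only in May 2023, about four months before the counts, so the pace may rise. The article does not exclude filling CR first and then seeking TAU participants. This stands, and it is why the point is tied to the observed pace and split and does not say that the target can never be met. It does not rescue the stated figures: Step 4 grants the best ordering and still falls short, and a faster pace alone does not change who declines CR.

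**The article condenses a fuller protocol.** A cap on CR or a separate TAU stream may be described there, so their absence from the article is not held against the plan. What is held against it is a size and a date printed beside counts that do not support them.

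**It is a pilot.** No power is claimed, and poor TAU uptake is something a pilot may legitimately discover. This also stands. The lack of a power calculation is no fault here, and the standard errors show loss of precision, not a missed power target.

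**Stronger readings that the documents do not support.**
- A reader might infer that group will be confounded with calendar time because TAU would be filled late. The article gives enrolment counts, not scan dates, and reports no change of scanner, raters or service. A shift that is stable over a participant's 12 weeks also cancels in the within-person change.
- A reader might infer that matching becomes impossible. A few TAU participants could each be matched to several CR participants; the result would be imprecise.
- A reader might apply the 30% upper limit to all 40 patients and conclude that TAU could reach about 12. Sixteen of those are already known, so about 8 is the right figure (Step 3).
- A reader might infer that the whole study fails. Hypotheses 1A and 1B do not use the CR-TAU contrast, nor does the before-after change within CR.

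**Conclusion.** The point holds. Under the stated allocation rule and the observed pace and split, 20 versus 20 by September 2024 is out of reach, and the realistic TAU size is about 2 with little prospect of more than about 5. This assumes that the TAU rate continues much as before, 16 months elapsed and 12 remaining, and no dropout, which would only make matters worse. None of the month ranges changes the conclusion.

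The consequence is confined to the between-group parts of the primary aim and of Hypotheses 2-4, and to the 2 x 2 ANOVAs. How serious it is depends on where TAU closes. At about 2 the contrast is close to uninformative and control-group mediation cannot be estimated. At 10 to 13 the standard error would be only about 1.2 times that planned: a weaker contrast, not a lost one.

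**What to change.** 1. Replace the stated size and date with an expected TAU number and completion date worked out from observed accrual. Alternatively, keep 20 and state how TAU recruitment will change to reach it.
2. Fix now, before outcomes are compared, a minimum TAU number. If the group closes below it, report CR-versus-TAU results as estimates with 95% confidence intervals only, and do not declare the between-group parts of Hypotheses 2-4 supported or refuted. The investigators should choose the number and give their reason; the table above shows the precision that each choice buys.

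Both are changes of wording, with no new assessments. The cost is an open acknowledgement that the between-group question may stay unanswered in this pilot.

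Widening the source of TAU participants beyond those not interested in CR is an option for the investigators, not a required change. It would be a protocol modification to be reported to the ethics committee, and the article documents neither a queue of patients waiting for CR nor a scan budget from which to judge it. If it is wanted, it has to be decided while recruitment is open, because a comparison group that was never enrolled cannot be supplied at analysis.

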## Discussion

### Principal Findings

CR has demonstrated effectiveness in improving neurocognitive functioning in individuals with SSDs; however, the mechanisms that mediate this effect remain unclear. This study describes the unique protocol for a pre-post pilot study that aims to investigate RL as a potential mechanism for improvement following CR. In this study, we predict that at baseline, individuals with schizophrenia will exhibit deficits in RL when compared with healthy controls. Further, we predict that these deficits will be more pronounced in learning tasks that involve social versus nonsocial stimuli. This would support previous research highlighting impaired reward processing in SSDs [8], particularly in social processing [19,20]. Social reward has significant impacts on the functional outcomes of this population, and there are no current interventions that target this problem, emphasizing the importance of this area of research. Moreover, difficulty in responding to feedback has been associated with cognitive function and negative symptoms in SSDs [15-17]. Thus, we propose that by reducing RL problems, we may in turn see a reduction in negative symptoms and an improvement in cognition.

The primary focus of this study is to investigate whether RL is improved after CR in individuals with schizophrenia. Only 1 other study has specially looked at the impact of CR on reward processing in SSDs [29], and results from this research suggest CR may improve response to feedback, moderated by the severity of negative symptoms. We believe CR serves to strengthen the processes involved in rewards and motivation that are needed for participants to persevere with difficult cognitive tasks via reinforcement of learning. Learning more about the way in which CR works is important to be able to maximize the effects of the intervention. Currently, CR is undertaken for around 3 months, with 2-4 sessions per week. Understanding the mechanisms of effect may enable improvements in the programs that enable more efficient delivery of this effective intervention.

### Limitations

The lack of blinding of researchers and the nonrandomized assignment of participants to conditions are limitations of the study design. Treatment allocation is based on individuals’ preferences to minimize attrition. As the intervention group is self-selecting, arguably, these participants may be better functioning than the patient control group. However, we believe that this will not necessarily be the case. For instance, some higher-functioning participants might select to be in the control group due to time restraints (ie, because of full-time study or work) limiting their ability to complete the CR therapy sessions. Nevertheless, we aim to recruit comparable participants from the patient control group and intervention group by matching for age, sex, and premorbid function across groups. There will also be some flexibility in the delivery of CR (ie, on the web vs in person and individual vs group), depending on participants’ access to the technology to run CR sessions and their preferences. This flexible mode of delivery was aimed at minimizing attrition, which has been an issue identified in the literature, in our work, and because of group therapy shutdowns during the COVID-19 pandemic [56,57].

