There is consistent evidence that people with SSDs are impaired at making rapid behavioral adjustments in response to feedback and that these impairments are associated with negative and cognitive symptoms [15-17]. Problems using the “fast system” are evident in situations requiring rapid change in responses to environmental changes when a situation previously rewarding begins to be associated with disadvantageous outcomes and oversensitivity to negative feedback and poor sensitivity to positive feedback. In contrast, several studies suggest that the gradual or procedural learning system seems intact in people with schizophrenia [18], but antipsychotic medication dosage, particularly for those with high levels of dopamine 2 receptor blockades, may exert a negative effect on this system.

Social environments are dynamic with constant rapid changes; hence, social situations require rapid behavioral adjustments in response to ever-changing social feedback. People with SSDs have impaired social functioning, and recent studies have shown that they also have impaired social reward processing [19,20]. Social approval induces rewarding feelings and is associated with increased activation in regions and networks associated with reward [21-23]. In those with SSDs, there is reduced activity in common reward brain regions during the experience of social reward [24], suggesting that they may have a reduced experience of the rewarding feeling of positive social attention. Positive social interactions have benefits for mental well-being and give life a sense of meaning [25]. Receiving praise and attention from others improves self-esteem [26] and increases motivation [27]. Although social reward has major impacts on functional outcomes, only recent efforts have explored social reward processing in SSDs. Further behavioral evidence suggests that RL difficulties are more pronounced in learning from positive, rather than negative, feedback [8]. This provides a further link between the effects of impaired RL and negative symptoms. Learning preferentially from negative outcomes is likely to lead to behavioral avoidance and social withdrawal, and have a negative impact on motivation. This hypothesis is supported by research suggesting that the magnitude of RL impairment, particularly for positive feedback, is associated with negative symptom severity [28].

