#### Demographic Information

At baseline, demographic and clinical information will be gathered, including sex, age, and date of birth. For the clinical groups, the case management team, primary and secondary diagnoses, mental health status, and list of current medications (name, dose, frequency, and route) will also be recorded.

A battery of validated assessment measures will also be delivered at baseline and follow-up for the clinical groups, as described in the subsequent sections.

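### Patients choose CR or TAU by interest in CR, and neither the stated matching nor the stated ANOVAs use the baseline motivation and dose data, so the 12-week contrast is open to confounding

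*Protocol article*

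**What the plan says.** All references are to the Protocol article.

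- **Allocation** (Participants, text after the exclusion criteria): "Those participants with SSDs (n=20) that are not interested in completing CR will form the patient TAU group". Group membership follows the patient's preference.
- **Acknowledged risk** (Limitations): "As the intervention group is self-selecting, arguably, these participants may be better functioning than the patient control group". The authors reply that this need not happen, because some higher-functioning patients may decline CR for lack of time.
- **Remedy offered** (Limitations): "we aim to recruit comparable participants from the patient control group and intervention group by matching for age, sex, and premorbid function across groups".
- **Comparative model** (Statistical Analysis): a 2 (group) by 2 (time) mixed ANOVA for each outcome measure, with no covariate named.
- **Dose** (Statistical Analysis): "medication dosages will be converted to olanzapine equivalents". No later use is stated. The Introduction (Overview) says that "antipsychotic medication dosage, particularly for those with high levels of dopamine 2 receptor blockades, may exert a negative effect on this system", where the system meant is the gradual or procedural one.
- **RL and fMRI comparison** (Statistical Analysis): second-level group analyses of the computational learning parameters and neural activity. Between-participant covariates are not described.
- **Data available**: CAINS (including avolition) and BIS/BAS (including drive and sensitivity to reward) are given to both patient groups at baseline and follow-up. Current medication is listed among the baseline clinical information.

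**The concern.** The article's own theory makes motivation a likely common cause of group and outcome. The Introduction counts reduced motivation among the negative symptoms, says that impaired reward processing leads to motivational deficits, and proposes that CR works through reward and motivation. Negative symptoms are an outcome, and RL is the proposed mediator. A patient's interest in a 12-week training programme is plausibly related to the same construct.

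The defence under Limitations deals with general functioning, and the matching variables are age, sex and premorbid function. Neither addresses motivation, negative symptoms, baseline RL or medication dose. If one of these also influences how much patients change over 12 weeks, a difference between CR and TAU can appear, or be hidden, without any effect of CR. The pilot is meant to lead to a larger randomized trial, so a misleading signal would carry forward into its planning.

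**Working it through.** **Plan's own figure.** The total of 60 reproduces as 20 + 20 + 20. The article reports no power calculation, so there is no power-based figure to reproduce.

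**What the stated test estimates.** With two time points, the group-by-time F test is the two-sample t test on change scores. A characteristic that shifts baseline and 12-week values equally cancels. One that also affects change does not.

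**Inputs.**
- From the article: n = 20 per patient group, so df = 20 + 20 − 2 = 38.
- Taken here: a two-sided 5% test (critical t = 2.024) and a true CR effect of zero.
- Assumed, not in the documents: gap *g* between groups in baseline motivation of 0.5 to 0.8 SD; correlation *r* of motivation with 12-week change of 0 to 0.5, with the SD of change set to 1.

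**Formulas.** Spurious effect = g × r, in SD of change. Noncentrality = (g × r) / √(1/20 + 1/20) = (g × r) / 0.316. The false-positive rate in favour of CR is the upper tail of the noncentral t with 38 df beyond 2.024.

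| g | r | spurious effect | noncentrality | false positive in favour of CR |
|---|---|---|---|---|
| any | 0 | 0 | 0 | 2.5% |
| 0.5 | 0.3 | 0.15 | 0.47 | 6.7% |
| 0.5 | 0.5 | 0.25 | 0.79 | 11.7% |
| 0.8 | 0.4 | 0.32 | 1.01 | 16.5% |
| 0.8 | 0.5 | 0.40 | 1.26 | 23.4% |

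If the product g × r is negative, the bias has the same size but works against CR.

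**Simulation check** (20 per group, 4,000 runs, true effect zero). With r = 0 the bias is about 0 and the two-sided error about 5% at every gap tried. With g of 0.5 to 0.8 and r of 0.3 to 0.5 the bias is 0.14 to 0.40 SD and the two-sided error 7% to 23%.

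**Scale.** At 20 per group the smallest effect with 80% power is 0.91 SD of change. The assumed bias is therefore 0.15/0.91 = 16% to 0.40/0.91 = 44% of it.

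**What adjustment achieves.** With a baseline motivation measure of assumed reliability 0.7, the remaining bias is g × r × (1 − 0.7), which is 0.15 × 0.3 = 0.045 to 0.40 × 0.3 = 0.12 SD. The simulation gave 0.04 to 0.12 SD and a two-sided error of 5% to 7%. Bias is reduced but not removed.

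**Why the baseline outcome should not be a main covariate.** Suppose the groups differ stably in the outcome by 0.5 to 0.8 SD and its retest correlation is 0.7 (assumed). Adjusting for the baseline value then creates a bias of gap × (1 − 0.7) = 0.15 to 0.24 SD, where the change-score test has none (Lord's paradox).

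**The case against.** The case on the other side has several parts.

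- **The limitation is disclosed, and this is a pilot.** True. The weakness lies in the remedy offered, since the risk itself was recognised.
- **Group-by-time already handles stable differences.** This stands, and bias needs an effect on change. The nearest evidence in the article is the one earlier CR study, where the severity of negative symptoms moderated improvement. That shows who responds to CR; it does not show change without CR, and no direction is given. It makes a link with change plausible without establishing it.
- **Covariates may sit in an analysis plan that is not shown.** This is fair for the second-level RL and fMRI analyses, which are left open. The ANOVA and the matching set are stated, however, and the matching is presented as the answer to self-selection.
- **The magnitudes are assumed.** They are, and the sign is open too: more impaired patients may have more room to improve.

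Some stronger readings are tempting but not supported:

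- That interest in CR is motivation itself. Limitations gives lack of time as another reason to decline.
- That the comparison is confounded as a matter of fact.
- That an unadjusted ANOVA would be the test of Hypothesis 2. The article assigns changes in learning efficiency to the second-level analyses, whose covariates are undescribed.
- That dose goes unused, or that dose changes are not captured. Both are inferred from silence: "At baseline, demographic and clinical information will be gathered" does not say that the medication list is not repeated.
- That the CR group is less heavily medicated, or that dose explains the fast-learning deficit. The dose remark concerns the gradual learning system, which the article describes as apparently intact.

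**Conclusion.** The concern holds in limited form. Allocation by interest in CR is plausibly related to motivation. The stated matching does not address motivation, negative symptoms, baseline RL or dose, and the stated ANOVAs name no covariate although suitable baseline data are available. The CR versus TAU contrast is therefore open to confounding of unknown size and sign.

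The illustration of 0.15 to 0.40 SD of change, with about 7% to 23% false positives favouring CR, rests wholly on the assumed gap and correlation, and it vanishes when motivation does not affect change. Because the limitation is disclosed and the study is a non-randomized pilot, this is a should-fix.

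**What to change.** 1. Keep the 2x2 ANOVA (change-score) estimate. Report beside it a pre-specified model of change with group, baseline CAINS motivation/pleasure (or a BAS score) and olanzapine-equivalent dose.
2. Apply the same covariates to the comparison of RL between the CR and TAU groups in the second-level analyses.
3. Use adjustment for the baseline value of the outcome only as a sensitivity analysis, because the groups are self-selected. Where CAINS is the outcome, the BAS score avoids overlap between covariate and outcome.
4. Where feasible, take baseline CAINS into account when filling the open TAU places. In September 2023 these were 20 − 1 = 19, against 15 patients already in CR, so close matching may be hard to achieve.
5. State that the medication list is repeated at the 12-week visit, so that dose change can be described.
6. Label the CR versus TAU contrast exploratory and state that residual confounding remains.

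The cost is some analysis wording, one repeated list at a visit already planned, and two degrees of freedom (38 to 36). No new instrument is needed.
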